#### Trial monitoring

Site level trial monitoring is being performed for protocol adherence and source data verification to the eCRFs. Additionally, central clinical research associates at the EPICENTER are performing centralized monitoring of the eCRFs. Serious adverse events are actively reviewed and monitored by the steering committee comprised of nephrologists. A formal Data and Safety Monitoring Board was not appointed for this study due to use of an approved device as the intervention. Any issues pertaining to nonadherence with eligibility of a randomized participant, allocation of interventions, or concerns relating to adverse events are being discussed with and reviewed by steering committee.

#### Dialysis, machines, and equipment

Each study site was provided with two dialysis machines capable of performing high volume online HDF (Fresenius 5008 CorDiax®). Sites are routinely supplied with dialyzers (Fresenius Polysulfone HDF 100®), bloodlines (Fresenius LifeLine_Beta_® adult bloodlines), and concentrates (Fresenius bibag® dry bicarbonate concentrate and liquid acid concentrate) for performing 6 months of HDF treatments for participants that were randomized to the high volume online HDF group. High-flux HD was performed using Fresenius 4008S machines, bloodlines, and concentrates used at the dialysis clinic sites for the run-in period and for patients randomized to the high-flux HD group; high-flux dialyzers (Fresenius FX Classix 100 (HD arm) and Fresenius Polysulfone HDF 100 (HDF arm)) were provided to the study sites for all study related treatments.

A Body Composition Monitor (Fresenius Medical Care, Bad Homburg, Germany) was supplied to the centers that did not previously have one to accurately monitor fluid status, measure body composition, and to determine the patients’ optimal post-dialysis weight for dialysis treatments performed in this trial. Both BCM and dialysis treatment data was captured in source documents and eCRF.

Investigators and clinical professionals at each participating center were trained by the study team in a standardized fashion to ensure there was homogeneity in dialysis treatment and study procedure. Routine study meetings are being performed for continuing training. This protocol recommends a standardized dialysis protocol following the current guidelines both for high flux HD or high volume online HDF. Postdilution high volume online HDF is being performed using the Fresenius 5008 CorDiax HDF machine with the AutoSub plus function and high-flux HD is being performed using the Fresenius 4008S machine. The recommended composition of the substitution fluids and dialysate was: sodium 138 mEq/L, potassium 2 mEq/L, calcium 1.5 mmol/L, dry bicarbonate 32 mEq/L and glucose 5.5 mmol/L. Dialysis needle size was standardized for high volume online HDF. For high volume online HDF, sterile and nonpyrogenic substitution fluids were produced by ultrafiltration of the ultrapure dialysate. The HD group also used ultrapure dialysate. Ultrapure quality was defined as bacterial counts < 0.1 CFU/mL and endotoxin levels < 0.025 EU/mL. Fresenius Polysulfone HDF 100 dialyzers are being used for high volume online HDF treatments and Fresenius FX Classix 100 dialyzers are being used for HD treatments. The intended dialysis treatment duration for both modality arms of the trial was 240 min. For the high volume online HDF arm, dialysis is being performed in the post-dilution mode with a target convection volume of 22 L/treatment.

#### Physical activity monitoring device

We are objectively measuring the patients’ physical activity levels over 7 days at the run-in and the 3- and 6-month follow up visits using a validated tri-axial accelerometer (ActiGraph™ wGT3X-BT model; http://www.actigraphcorp.com) that measures detailed parameters of physical activity [23, 35–38]. The ActiGraph™ is lightweight (19 g), worn at the waist, interfaces with the internet via Bluetooth, and date- and time-stamped activity levels are being uploaded at routine dialysis visits. Activity during sleep cannot be accurately determined with use of a waist worn physical activity monitor, therefore we ask patients to take off the physical activity monitor during sleep. Additionally, the physical activity monitor is being removed during bathing.

#### Diary logs

During the 7 days of physical activity monitoring patients are completing a diary that records the time of their dialysis treatment, sleep, bathing, and any time that they are not wearing the physical activity monitor. The physical activity monitoring has/is being started before the dialysis treatment in the run-in period, at the 3- and 6-month visit. Each patient is given a paper diary and instructed how to complete the diary by the investigator or their designee. On the first day of activity monitoring, the patients were given a diary with their study patient number denoted on it and they record their age, weight, and height; the investigative staff assisted patients in completion of their information as needed. Throughout the 7 days of activity monitoring, patients recorded the start and end time of dialysis (on dialysis days), the time they go to sleep and wake, the time they start and end bathing, and any time that they did not wear the physical activity monitor for more than 30 min.

#### HRQOL questionnaires

HRQOL is being assessed at the baseline and follow-up study visits with the Kidney Disease Quality of Life - Short Form (KDQOL-SF) version 1.3 that has been adapted and validated to Brazilian Portuguese [39]. The KDQOL-SF consists eight domains that can be summarized in two summary scores, one for physical functioning (the physical composite score (PCS)) and one for mental functioning (the mental composite score (MCS)). After initiation of the study, it was identified that there was one question in the KDQOL-SF survey that had a typographical error in up to 100 surveys; this question was supposed to read as follows: “do you get sick a little easier than other people?”. However, the typographical error made the question ask patients “do you get obey a little easier than other people?”. After identification of the error in this survey, study coordinators adjudicated and corrected the patients’ response to the question answer if it was incorrect.

In addition, HRQOL is being assessed by the Time to Recover from Dialysis Question, “How long does it take you to recover from a dialysis session?”; patients could answer a time in minutes after dialysis. This question has been shown to have both convergent and divergent validity in HD patients, and demonstrated to be sensitive to change [40]. Moreover, participants will also have HRQOL assessed via Dialysis Thirst Inventory, which is a seven-item questionnaire that five point Likert type scale for each item (never = 1, almost never = 2, sometimes = 3, often, very often = 5) [41]. The Dialysis Thirst Inventory has been shown in an RCT to be positively correlated to interdialytic weight gain [42], and found to have consistent detection of thirst/dry mouth as the validated Xerostomia Inventory (XI) [41]. All questionnaires will be administered to patients by staff who will help the patients to fill out the forms, if necessary.

#### Biomarker laboratory specimens

Pre- and post-dialysis study specific blood specimens were collected at the randomization visit and will be collected at the 3- and 6-month follow up visits for biorepository and exploratory analysis of biomarkers of inflammation, oxidative stress, and uremic toxins. These include the collection of 8–10 mL of blood in two different tubes (serum and plasma), processing and storage at the temperature of − 20 C by the clinic team. All biomarker specimens are transferred to the central lab and stored at − 80 C (PUCPR Multiuser Core Facility: [name]).

### Power analysis

Data will be analyzed according to an intention-to-treat principle (i.e. according to assigned instead of received treatment). The primary endpoint is steps per 24 h beginning at the start of each dialysis treatment on dialysis days and concurrent times on non-dialysis days in patients treated with high volume online HDF versus high-flux HD. With an enrollment target of 110 participants in each arm (considering a drop out of 20%) we estimated the 86 patients will complete the follow up in each arm, which will provide the trial a 90% power to detect a 20% effect with respect to the primary outcome (predefined as a 20% increase in average total steps at the dialysis day in the high volume online HDF group compared to the high flux HD group).

In addition, near the end of the baseline period we confirmed the power calculation using interim baseline data (*n* = 142); this computation suggested that enrollment of 120 subjects would be anticipated to detect a 10% effect with respect to the primary outcome with 90% statistical power, and with 90 subjects it would be anticipated to detect an effect with respect to the primary outcome with 80% statistical power.

### Physical activity analysis

Accelerometry continuously records data over 7 days of activity monitoring. Physical activity data in this study is being extracted from the accelerometer files for times relative to the beginning of dialysis to 24 h after the initiation of dialysis, and concurrent/parallel times to dialysis on the following first non-dialysis days and the second long interdialytic non-dialysis day. We are extracting data from the physical activity monitor using the ActiLife v6.13.3 software (http://actigraphcorp.com/support/software/actilife/). Raw physical activity data is uncompressed and bandpass filtered using the default filter with an epoch length of 60 s. The validation and filtering non-wear time readings is being performed using vector magnitude and the Choi 2011 algorithm [43], with the custom setting of 60 min for the window of consecutive zero or non-zero measurements [44]. Notably, we did test the utility of the low frequency filter available with the ActiGraph activity monitor yet identified overcounting with discrepancies of more than 2000 steps per hour in some instances compared to the default filter.

The physical activity levels are cleaned, sliced, computed and exported from the ActiLife software using a custom coded file to denote predefined granular slices based off the start and end time of each dialysis session for each patient, as well as concurrent/parallel times to dialysis on the following first non-dialysis days and the second long interdialytic non-dialysis day. For the computation physical activity levels, we are using the Freedson VM3 Combination (2011) algorithm to calculate energy expenditure and most moderate to vigorous physical activity (MVPA) level cut points [45], as well as, the Freedson Adult 1998 algorithm to calculate the metabolic rates (MET) [46]. The cut points used for physical activity levels of MVPA are as follows: Sedentary = 0–99 counts per minute (CPM); Light = 100–2689 CPM; Moderate Activity = 2690–6166 CPM; Vigorous = 6167–9642 CPM; Very Vigorous = 9643-infinity CPM. We defined bouts of physical activity being as 10 consecutive minute periods of MVPA and sedentary bouts as 10 consecutive minute periods of no physical activity. In instances that patients do not adhere to the protocol and wore the physical activity monitor during sleep, we code the export files to exclude this protocol defined non-wear time from the activity data using the sleep times reported by the patient in their diary log.

To allow for the assessment of granular physical activity levels relative to the timing of dialysis, the data is being extracted from the accelerometer files in predefined periods in 3 blocks (A, B, C) consisting of a total of 9 slices for each 24-h period on dialysis days (0 to ≤24 h after dialysis start; Fig. 2), first non-dialysis days (> 24 to ≤48 h after dialysis start; Fig. 3), and the second long interdialytic non-dialysis day (> 48 to ≤72 h after dialysis start; Fig. 4).

**Fig. 2 Fig2:**

Schematic of Slicing of Physical Activity Data on Dialysis Days

**Fig. 3 Fig3:**

Schematic of Slicing of Physical Activity Data on Non-Dialysis Days

**Fig. 4 Fig4:**

Schematic of Slicing of Physical Activity Data on Long Interdialytic Day

The extraction of data in Block A captures per patient physical activity data during dialysis (approximately 0 to ≤4 h after dialysis start), or data from concurrent/parallel times to dialysis on the subsequent first non-dialysis days (> 24 to ≤28 h after dialysis start) and second long non-dialysis day (> 48 to ≤52 h after dialysis start). Block A contains one slice of data.

The extraction of data in Block B captures per patient physical activity data starting the minute after completion of dialysis to 2 h post-dialysis (> 4 to ≤6 h after dialysis start), or data from concurrent/parallel times on the subsequent first non-dialysis days (> 28 to ≤30 h after dialysis start) and second long non-dialysis day (> 52 to ≤54 h after dialysis start). Block B has 4 predefined data slices of 30 min each in the 2-h period.

The extraction of data in Block C captures per patient physical activity data starting 2 h post-dialysis to 20 h post-dialysis (> 6 to ≤24 h after dialysis start), or data from concurrent/parallel times on the subsequent first non-dialysis days (> 30 to ≤48 h after dialysis start) and second long non-dialysis day (> 54 to ≤72 h after dialysis start). Block C has 4 predefined data slices of 4.5 h each in the 18-h period. The last 4.5-h slice in Block C may be truncated or extended to the start time the following dialysis session, if applicable.

### Statistical design

For the analysis of study data, we plan to perform descriptive calculation and tabulation of the average profiles of recruitment, demographics, clinical parameters, and physical activity levels. The distribution of physical activity levels (e.g. steps per 24 h and MVPA) will be computed and analyzed for normality using histograms and Kolmogorov Smirnoff normality test. Average values for all categorical variables will be calculated in counts or proportions. Continuous variables will be determined by calculating the mean with the standard deviation (SD) or median with 25th and 75th percentile. We plan to report physical activity levels by the 24-h post-dialysis period on dialysis days, as well as on concurrent periods on non-dialysis days and the long interdialytic day.

In subgroup analyses, we plan to establish granular profiles of physical activity levels after dialysis treatments, which will include analyses that explore if there are any differences between the dialysis days, non-dialysis days and the long interdialytic day, as well as differences between the first, second and third dialysis session of the calendar week. We plan to perform additional subgroup and exploratory analysis to investigate if differing demographic, clinical, laboratory, treatment, and other parameters influence physical activity levels. Further analysis may include additional profiles of energy expenditure (e.g. kilocalories, metabolic equivalent of task (MET) rates), body position (e.g. sitting, standing, walking), and other metrics available from the activity monitor.

We plan to perform an explorative analysis of missing treatments and missing data to evaluate if missing completely at random (MCAR), missing at random (MAR) or missing not at random (MNAR). Complete case analysis and multiple imputation will be considered based on frequency of missing data and nature of missing patterns.

The hypothesis driven outcomes of this study include the:Primary outcome: the difference in the change in steps per 24 h on dialysis days (captured by a triaxial accelerometer and in reference to the start time of the dialysis) from baseline to the 6-month follow up in patients treated with high volume online HDF versus high-flux HD.Secondary outcome: the difference in the change in KDQOL scores (total, PCS and MCS) and self-reported dialysis recovery time from baseline to the 6-month follow up in patients treated with high volume online HDF versus high-flux HD.Various exploratory and subgroup outcomes will also be assessed to investigate hypotheses.

For the primary outcome of step counts per 24 h, we plan to use an intention-to-treat design to determine the effect of the intervention using linear mixed effects model comparing mean changes from baseline between treatment groups at months 3 and 6 with data presented in box-plots and histograms for the baseline, 3- and 6-month study periods. Similar methods will be used to assess exploratory HRQOL and other outcomes. Further evaluation of statistical interaction between the treatment effect on primary outcome may be performed for age, sex, body composition and other parameters.

An exploratory as-treated analysis may also be performed on the primary outcome, which will be restricted to those that achieved the target convection volume of 22 L per treatment at most dialysis sessions and did not miss a remarkable proportion of their dialysis treatments. This analysis will be performed using the same methods as the intention-to-treat analysis. Adjustments may be performed to the analysis via inverse probability weighting and g-estimation methods.

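### The missing-data plan sets out to judge MAR against MNAR from the data, which observed data cannot show, and does not tie its options to the primary mixed model

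*Protocol article*

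**What the plan says.** All references are to the protocol article.

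- **Statistical design, missing data.** The section announces an exploratory look at "missing treatments and missing data to evaluate if missing completely at random (MCAR), missing at random (MAR) or missing not at random (MNAR". The next sentence reads "Complete case analysis and multiple imputation will be considered based on frequency of missing data and nature of missing patterns". It gives no default method and no threshold.
- **Statistical design, primary outcome.** The primary analysis of steps per 24 h is a "linear mixed effects model comparing mean changes from baseline between treatment groups at months 3 and 6", described as intention-to-treat. The text does not say whether complete-case analysis or imputation would replace, feed or accompany this model.
- **Power analysis.** "Data will be analyzed according to an intention-to-treat principle (i.e. according to assigned instead of received treatment". The same section plans for losses: "With an enrollment target of 110 participants in each arm (considering a drop out of 20%) we estimated the 86 patients will complete".
- **Early withdraw/discontinuation.** Follow-up goes on after the interventional treatment is stopped, unless the patient is withdrawn from the study. Nothing more is collected after consent is withdrawn, so some month-6 values will be missing.

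**The concern.** A missing-data plan has to name an assumption, because the data cannot supply one. This plan treats the mechanism as something to be found out by exploration. Evidence against MCAR can be found that way, by relating dropout to baseline or month-3 steps. The distinction between MAR and MNAR depends on the values that were not observed, so the planned evaluation cannot return the answer it promises.

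The two options then offered do not cover the ground. Complete-case analysis discards a randomised patient who has baseline and month-3 steps but no month-6 value, and it can be biased under MAR. Multiple imputation in its standard form assumes MAR, so it does not help if MNAR is suspected. Meanwhile the article already names a model that, fitted by likelihood, keeps the partial records and is valid under MAR. Because the two paragraphs are not connected, a reader cannot tell which assumption the primary result will carry. At stake are some loss of information, avoidable bias if dropout differs between arms, and no stated way to judge robustness to MNAR.

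**Working it through.** **1. The plan's own figures.** From Power analysis: 110 per arm, 20% dropout, 86 completers.

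- Forward: 110 × (1 − 0.20) = 88, against 86 stated.
- Backward: 86 / (1 − 0.20) = 107.5, so 108, against 110 stated.

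These agree to within two patients. A complete-case analysis would therefore leave out 110 − 88 = 22 to 110 − 86 = 24 patients per arm. On the 195 patients enrolled (Study status and timeline), 20% is 0.20 × 195 = 39. The article does not say how many of them would have month-3 steps.

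**2. Why MAR and MNAR cannot be told apart.** In one arm let π be the proportion missing at month 6. Then

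arm mean = (1 − π) × (mean of those observed) + π × (mean of those missing).

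Write the last mean as the value predicted from baseline and month 3, plus δ. MAR implies δ = 0; a non-zero δ is MNAR. Every observed quantity is the same whatever δ is, yet the arm mean moves by π × δ. With π = 0.20 and an assumed δ of 0.25 to 0.75 SD in one arm only:

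- 0.20 × 0.25 = 0.05 SD
- 0.20 × 0.75 = 0.15 SD

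The contrast shifts by that amount and no exploration of the observed data can reveal it.

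**3. What the options do under each mechanism.** This is an illustrative simulation with all values assumed: 400,000 patients, true effect 0, 20% missing at month 6 overall, baseline-SD units. Month 3 = 0.6 × baseline + 0.8 × noise. Month 6 = 0.2 × baseline + 0.55 × month 3 + 0.7 × noise. In the MAR and MNAR scenarios, the log-odds of a missing value in one arm fall by 1 per unit of steps; in the other arm they are constant. Complete case is a regression of change on arm and baseline in patients with a month-6 value. The MAR-based method is regression imputation within arm from baseline and month 3, standing in for multiple imputation or a likelihood mixed model in large samples.

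| Missingness | Complete case | MAR-based |
|---|---|---|
| MCAR | 0.00 | 0.00 |
| MAR, driven by month 3 | 0.07 | 0.00 |
| MNAR, driven by month 6 | 0.13 | 0.10 |

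The excess bias of complete case over the MAR-based method is 0 under MCAR, 0.07 SD under MAR and 0.134 − 0.102 = 0.03 SD under MNAR. Most of the MNAR bias remains under the MAR-based method, so MNAR needs a sensitivity analysis of its own.

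**4. Scale against the design effect.** The article states "90% power to detect a 20% effect with respect to the primary outcome" and gives no SD, alpha or sidedness. At an assumed two-sided alpha of 0.05, 86 per arm and 90% power imply 3.24 × √(2/86) = 0.49 SD. That figure is back-solved. Its SD may not be the baseline SD used in step 3, so the biases above are not expressed as a share of the planned effect.

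**The case against.** The strongest reply is that the primary analysis is already fixed. The mixed model is named, the missing-data sentences cover study data in general, and nothing says that complete case would replace the model. The exploratory step is only exploratory, and a separate analysis plan may settle the rest.

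Part of this stands. An article may leave detail to a plan that is not shown, and the absence of an MNAR analysis would not by itself be a fault. But the mechanism evaluation and the two candidate methods are stated text, and what is stated cannot work as described.

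Four stronger readings are tempting, and the document does not support them.

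- **That complete case breaks the stated intention-to-treat principle.** The article defines the principle as analysis by assigned arm, which a complete-case analysis can satisfy. What can be said is that it falls short of using all randomised patients.
- **That there is a firm either/or rule driven by a MAR or MNAR verdict.** The wording only says that both methods will be considered, in the light of how much is missing and in what pattern. They could be run side by side.
- **That the choice follows sight of the outcomes by arm.** The article gives no timing. It explains the lack of blinding for investigators and local clinical staff, and does not describe analysts' access to results by arm.
- **That the bias is a fixed fraction of a planned 0.5 SD effect.** No such effect is stated, for the reasons given in the working.

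It is also fair to add that continued data collection after stopping the intervention limits the amount of missing data.

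**Conclusion.** The point holds in this form: the stated evaluation cannot separate MAR from MNAR and so cannot guide the choice of method; complete case can be biased under MAR; standard multiple imputation does not address MNAR; and neither option is related to the named mixed model. These conclusions need no figures.

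The size is uncertain. At the planned dropout, 22 to 24 of 110 patients per arm would be dropped by a complete-case analysis. The simulated excess bias over a MAR-based method, 0 to 0.07 SD, depends on the assumed correlations, on 20% missing, and on outcome-related dropout in one arm only. The 0.05 to 0.15 SD shift depends on an assumed δ in one arm. None of these is an estimate for this trial. The flaw is a poorly fixed procedure that is cheap to repair. It does not show that the primary analysis is invalid, because the mixed model, fitted by likelihood to all observed data, would be a sound primary choice under MAR.

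**What to change.** Replace the two missing-data sentences with text to this effect:

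> The primary analysis is the linear mixed effects model fitted by maximum likelihood to all observed baseline, month-3 and month-6 step counts of all randomised patients, by assigned arm, assuming MAR. Frequencies and patterns of missing data are described by arm and do not determine the method. Any complete-case analysis is supportive only. Sensitivity to MNAR is examined by multiple imputation with a delta adjustment applied separately by arm over a range fixed in advance.

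The cost is wording and one extra sensitivity analysis. It needs no new data and no change to visits. The article reports that follow-up was still under way, so the assumption could be fixed before the final analysis.

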### Study visit procedures

#### Screening and run-in

Patients who were potential candidates for the HDFIT trial were invited by the investigators to be screened for eligibility; those confirmed to be eligible were approached for recruitment. The investigator reviewed the informed consent form (ICF), study procedures, risks, and benefits with each patient. In addition to study procedures, the ICF also included the details on the collection of biorepository specimens for use in ancillary studies of biomarkers (e.g. MMW toxins). Interested patients provided their signed consent on two copies of the ICF; both ICFs were signed and executed by the investigator. One of the two executed ICFs was filed in the patient’s medical record and the other was given to the patient for their records.

After signing the ICF, participants entered the screening and run in period for a period for up to 4 weeks. During the screening and run-in period patients receiving high-flux HD as a standard of care continued to undergo high-flux HD and could have baseline assessments captured and move onto enrollment. Patients using low-flux HD as a standard of care were switched to high-flux HD for the full 4-week run in period. All HD treatments during the screening and run in period were performed using standardized high-flux dialyzers. Baseline physical activity levels were objectively measured over 7 days during the screening and run-in period. Baseline demographic, clinical, and social data were recorded from the patient’s standard of care medical records, the investigator assessments, and/or per patient report. Baseline parameters recorded in the screening and run-in period included: demographics (age, sex, race) social parameters (educational level, family income level, employment status, transportation method to clinic, distance from the clinic to the patient’s residence), dialysis access type (arteriovenous fistula, graft or permanent catheter), clinical characteristics (height, weight), and treatment characteristics. The investigators reviewed the patients’ medical history, clinical case, and laboratory data during the screening and run-in period; those identified by the investigator to meet all inclusion and no exclusion criteria were scheduled to proceed to be randomized into the trial.

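### The primary mixed model is worded as a comparison of changes from baseline with no stated adjustment for baseline steps; stating that adjustment is a free gain in precision

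*Protocol article*

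**What the plan says.** In the protocol article, Statistical design defines the primary outcome as "the difference in the change in steps per 24 h on dialysis days" from baseline to month 6, HDF against HD. The planned intention-to-treat analysis is a "linear mixed effects model comparing mean changes from baseline between treatment groups at months 3 and 6". No model terms are listed, so baseline adjustment is neither stated nor excluded. The same section says that similar methods will serve the HRQOL and other outcomes.

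The baseline value exists and precedes allocation. Screening and run-in states: "Baseline physical activity levels were objectively measured over 7 days during the screening and run-in period".

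Power analysis is written in terms of the step level: "The primary endpoint is steps per 24 h beginning at the start of each dialysis treatment on dialysis days". The target effect is "predefined as a 20% increase in average total steps at the dialysis day in the high volume online HDF group" relative to the HD group, and 86 completers per arm are expected, "which will provide the trial a 90% power to detect a 20% effect with respect to the primary outcome". The section then reports a re-check on baseline data from 142 patients: 120 subjects for a 10% effect at 90% power, and 90 subjects for 80% power. No SD, mean, alpha, sidedness or correlation is given for either calculation.

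**The concern.** An unadjusted change score subtracts the whole baseline value, which fixes the baseline slope at 1. When the correlation between baseline and month 6 is moderate, the best slope is well below 1, so subtracting the full baseline adds noise. Adjusting for baseline lets the data choose the slope and is never less precise in large samples. Since baseline steps are measured before randomisation, the gain needs no new data.

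What is at stake is the width of the confidence interval for the primary comparison, and for the secondary outcomes if the same wording carries over to them. It also matters that the re-check of power used baseline data only. Such data cannot supply the SD of a 6-month change or the correlation that links it to the SD of the level.

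**Working it through.** **Inputs from the protocol article.** 110 enrolled per arm, 20% dropout, 86 completers per arm, 90% power, 20% effect; re-check figures of 120 and 90 subjects for 90% and 80% power (Power analysis); 195 actually enrolled (Study status and timeline).

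**Assumptions, not in the article.** Two-sided alpha 5%, normal approximation, complete data, ρ of 0.3, 0.5 and 0.7, and SDs back-solved below and treated as cross-sectional.

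**1. The plan's own figures.** 110 × 0.8 = 88, within two patients of the stated 86. The 90% power cannot be reproduced without an SD. Solving for it: d = (1.960 + 1.282) × √(2/86) = 0.494, so SD = 0.20/0.494 = 40.5% of the mean.

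The re-check implies something else. For 80% against 90% power, the ratio of sample sizes is (2.802/3.242)² = 0.747, and 120 × 0.747 = 89.6, so the 120 and 90 agree with each other. For a 10% effect they imply:
- 120 in total (60 per arm): d = 3.242 × √(2/60) = 0.592, SD = 0.10/0.592 = 16.9% of the mean.
- 120 per arm: d = 3.242 × √(2/120) = 0.418, SD = 0.10/0.418 = 23.9% of the mean.

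**2. Variance of the month-6 estimate.** Let s₀ and s₁ be the SDs at baseline and month 6.
- Unadjusted change: s₀² + s₁² − 2ρs₀s₁, which is 2(1−ρ)s² when the SDs are equal.
- Baseline-adjusted: s₁²(1−ρ²).
- The first minus the second is (s₀ − ρs₁)², which is never negative.
- With equal SDs, the ratio of adjusted to change is (1−ρ²)/(2(1−ρ)) = (1+ρ)/2.

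| ρ | change, 2(1−ρ) | adjusted, 1−ρ² | ratio | reduction |
|---|---|---|---|---|
| 0.3 | 1.40 | 0.91 | 0.65 | 35% |
| 0.5 | 1.00 | 0.75 | 0.75 | 25% |
| 0.7 | 0.60 | 0.51 | 0.85 | 15% |

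A simulation of the month-6 comparison (4,000 runs, 86 per arm, complete data) gave 1.44 and 0.91, 0.98 and 0.75, and 0.59 and 0.50 for change and adjusted. Regressing the change on treatment and baseline gave the same treatment estimate as regressing the month-6 level on them.

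**3. Power for a 20% effect.** 195/2 × 0.8 = 78 completers per arm. Power = Φ(0.20/(SD × √factor) × √(78/2) − 1.960), with the factor from the table.

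| SD, % of mean | ρ | change | adjusted |
|---|---|---|---|
| 40.5 | 0.3 | 74% | 90% |
| 40.5 | 0.5 | 87% | 95% |
| 40.5 | 0.7 | 98% | 99% |
| 23.9 | 0.3 | 99% | >99% |
| 16.9 | 0.3 | >99% | >99% |

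At an SD of 23.9% and ρ = 0, the unadjusted change still has 96% power.

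**4. Power for the 10% effect quoted in the re-check, 78 per arm.** With SD 23.9%, change against adjusted is 60% against 78% at ρ = 0.3, 74% against 85% at 0.5, and 92% against 96% at 0.7. With SD 16.9% it is 88% against 97%, 96% against 99%, and above 99% for both.

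**The case against.** The strongest reply is that the article never says baseline is left out. Comparing mean changes describes a contrast. It is compatible with a model of change that includes baseline as a covariate, which gives the same treatment estimate as the recommended analysis, and with a model that constrains the baseline means to be equal. Covariate lists are commonly left to an analysis plan, which is not shown here. This stands in part: the lack of adjustment is inferred from the wording. But the article does word the primary comparison, and someone following it literally would arrive at the unadjusted change.

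A change comparison is also unbiased in a randomised trial, and chance baseline imbalance is already counted in its variance. That stands, so imbalance is not claimed as a separate harm. Likewise, randomisation makes the expected month-6 difference in level equal to the expected difference in change. Stating the effect as a level and the outcome as a change is therefore not in itself a contradiction; only the SD may differ.

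A reader might infer that the stated 90% power is reached only if ρ is at least 0.5, the value at which change and level have the same variance. The documents do not support that. It would require that the trial was sized on a cross-sectional SD of about 40% of the mean, that variances are equal over time and that baseline is absent from the model. If the sizing SD was already that of change, no such threshold exists. With the SD implied by the re-check, a 20% effect is well powered even at ρ = 0.

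**Conclusion.** The point holds as an improvement in precision. Followed literally, the worded analysis gives a month-6 estimate whose variance exceeds what baseline adjustment would give. Adjustment lowers it by 35%, 25% or 15% at assumed ρ of 0.3, 0.5 or 0.7, with equal variances over time. That adjustment is never worse does not depend on equal variances, apart from the negligible cost of estimating one slope in about 156 completers.

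The consequence for power stays open. It ranges from substantial for the 20% effect (SD about 40% of the mean, low ρ) to almost none (SD 17–24%). The article's two power statements imply different SDs and give none, so neither end can be ruled out. No failure of the stated 90% power is shown. If an unseen analysis plan already includes baseline, all that remains is to say so in the article's description.

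**What to change.** Replace the sentence on the primary analysis in Statistical design with one that states: a linear mixed model of dialysis-day steps at months 3 and 6, with treatment, visit, treatment by visit, baseline steps and baseline by visit; or a model with baseline as a response and the baseline means of the two arms constrained equal. Name the month-6 adjusted mean difference as the primary estimate. Use the same form for the KDQOL scores and recovery time, each with its own baseline value.

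The cost is a sentence of wording. The baseline measurements are already part of the protocol, and no visit, procedure or patient is added. The wording should be settled before the arms are compared. Giving the SD, alpha and any correlation behind the power statement would also let a reader see how much the choice matters.
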